#### Confidentiality {27}

To ensure confidentiality, all participants will be allocated a unique coded ID number, which will be used to identify them throughout the trial.

Personal data held electronically will be stored on a data management system which will be accessible to delegated members of the coordinating team via individual password. Paper forms containing participant identifiable information (e.g. patient details form and consent form) will be held separately to questionnaire data in a locked filing cabinet, in an office only accessible via registered swipe card access held by the YTU research team. Photographs to record wound healing will be anonymised prior to electronic transfer by sites to YTU, where the image will be stored in an encrypted and password protected drive. All data will be stored and handled in accordance with data protection principles.

To ensure that the study is carried out correctly, participants’ data may be reviewed by members of the research team or other authorised people, maintaining confidentiality at all times. Participants will consent to this review of their data at the start of the study. Identifying information will be removed before the data is analysed and the results presented and published.

#### Plans for collection, laboratory evaluation and storage of biological specimens for genetic or molecular analysis in this trial/future use {33}

There will be no biological specimens collected within the SWHSI-2 trial; therefore, no plans are required for collection, evaluation or storage of such specimens.

### Statistical methods

#### Statistical methods for primary and secondary outcomes and additional analyses {20a, 20b}

##### Statistical analysis

Outcome analyses will be conducted following the principles of intention-to-treat with participant’s outcomes analysed according to their original, randomised group. Analysis will be undertaken using Stata version 16 or later (College Station, TX: StataCorp LLC). Significance tests will be two-sided at the 5% significance level, and parameter estimates will be presented with associated 95% CI and *p*-values as appropriate.

Baseline data will be summarised by randomised group, as randomised and as included in the primary analysis [31], using descriptive statistics for continuous variables and count and percentage for categorical variables. No formal statistical comparison of baseline data will be made between the groups.

For the primary outcome of time to healing of the reference wound (derived as the difference in days between randomisation and the first date of complete healing), healing rates will be presented overall and by trial arm. Kaplan–Meier survival curves will be produced for the two groups and the median time to healing with a 95% CI presented. A proportional hazards Cox regression model will be used to compare the healing times between the two groups, adjusting for wound size at baseline, duration of wound in days (time between wound start date and randomisation), and wound location as fixed effects, and centre as a shared frailty effect.

Secondary outcomes, including adverse events, will be analysed where appropriate using regression techniques appropriate for the type of data.

Full details for the statistical analysis will be provided in a statistical analysis plan, which will be prepared prior to the completion of data collection.

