## Introduction

### Background and rationale {6a}

More than 10 million surgical operations are performed in the NHS every year [1].Wounds are usually closed by apposing the wound edges — “healing by primary intention”. However, when closure is not possible, or when primarily closed wounds break down (dehisce), they are usually left open to heal from the bottom up, through formation of granulation tissue — “healing by secondary intention”.

Surgical wounds healing by secondary intention (SWHSI) are a common, complex problem. A recent survey estimated the UK prevalence of SWHSI to be 4.1 per 10,000 population and identified colorectal, plastics and vascular as the surgical specialties most commonly associated with SWHSI [2].

Treatment of these wounds presents a significant financial burden to the NHS, with costs of SWHSI estimated to be £1060 per patient, before inclusion of treatment costs [3]. The healing pathway of SWHSI patients is often prolonged and complex with a variety of treatment options, ranging from basic, relatively inexpensive wound dressings (around £441 per month) to complex, expensive treatments such as Negative pressure wound therapy (NPWT, around £1323 per month [4]).

These wounds pose a unique management challenge and difficulties for patients; they can remain open for many months, may require a multitude of treatments, are highly susceptible to infection and may require prolonged hospitalisation and/or further operations [5]. The healing pathway of patients with an open wound is often prolonged, which has a substantial impact on health-related quality of life [6, 7]. In a recent cohort study of 396 people undergoing SWHSI, the median time to healing was 86 days (95% confidence interval (CI) 75 to 130). In specific wound sites (e.g. foot/leg), the duration was almost double that of wounds elsewhere on the body [8]. Infection (32.1%), hospital readmission (24.7%) and further surgical procedures (16.8%) were all common [8]. People with SWHSI often require frequent dressing changes, and for many years standard dressings that filled cavities and/or covered open surgical wounds were used widely. More recently negative pressure wound therapy has been introduced and seen rapid increased use: a recent UK-based survey and cohort study of SWHSI found an increase from 6 to 29% in a 1-year period [4].

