#### Exclusion criteria

Life expectancy of less than 6 months, e.g. undergoing end stage palliative careActive systemic infection (including osteomyelitis) at baseline as defined by clinical and/or laboratory assessment. Note: Patients who have an active infection, but are improving following 1 week’s duration of antibiotics, may be included at the healthcare professional’s discretion.Inadequate haemostasis or patients who are at risk of bleedingChronic wounds non-surgical in origin (e.g. pressure ulcers or foot ulcers*)*Note: diabetic foot ulcers that have been incised and drained or debrided as an inpatient in theatre may be included given this constitutes a surgical woundCurrent open wound has previously been, or is currently being, treated with NPWT.Planned delayed primary closure of the woundContraindication to NPWT including the following:
Presence of unclear undermining in the wound cavity (i.e. the deepest point of the wound cannot be measured)Presence of necrotic tissue, malignant tissue or escharWounds involving exposed blood vessels and/or organs, anastomotic sites and/or nerves (including the “open abdomen” where the abdominal fascia is open)Wounds situated where, in the opinion of the treating healthcare professional, a vacuum seal cannot be obtainedPresence of a non-enteric or unexplored fistulaPeople requiring emergency airway aspiration, pleural mediastinal or chest tube drainage or surgical suctionCurrently participating in another wound research study, where the primary outcome has not yet been reached

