### Outcomes {12}

#### Primary outcome

The primary outcome for SWHSI-2 is time to healing (defined using the clinical criterion “complete epithelial cover in the absence of a scab”) in days from randomisation.

Participants will be contacted weekly by a research nurse and asked if a healthcare professional has indicated that their wound has healed and whether this meets the healing definition (i.e. there is full coverage and no scab present). If the participant believes the wound is healed, but this has not been confirmed by a healthcare professional, the research nurse will seek confirmation/further information from the clinical team.

Once healing has been confirmed, participants will undergo clinical assessments on 3 subsequent consecutive weeks to confirm continued wound healing. A standardised photograph will be taken of the wound at the first healing assessment. Participants (with assistance from family/friends if necessary) will also be asked to take a digital photograph of the wound themselves and submit this to the study team. Study specific instructions will be provided to facilitate this.

Given the subjective nature of healing assessment (23), the photographs will be used to facilitate additional outcome (time to healing) verification by clinically experienced, independent, blinded observers.

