#### Secondary outcomes

Secondary outcomes are as follows:
Clinical events including antibiotic treatment, hospital admission or discharge, treatment status (including reasons for dressing or treatment failure or change), re-operation (including skin grafting and closure surgery*), amputation and death. Details of any clinical events experienced will be collected during the weekly telephone follow-up.Wound infection using a modified Bluebelle Wound Healing Questionnaire (WHQ) [17, 18]. This will be completed by the participant at baseline, 3-, 6- and 12-month follow-up assessments and at the initial healing visit. The WHQ will be modified for relevance to patients with open wounds by removing three items relating to spontaneous or deliberate wound dehiscence and use of dressings given these would not be relevant in this population. The time frame for the questionnaire will also be adapted to reflect the questionnaire should be completed since the participant had their open wound (baseline and wound healing, or since the last Bluebelle questionnaire was completed (months 3, 6 and 12) rather than from the time since hospital discharge.Pain using a visual analogue scale (0 = no pain — 10 = worst imaginable pain). This will be completed by the participant at baseline, 3-, 6- and 12-month follow-up assessments.Health-Related Quality of life using the EQ-5D-5L [19]. This will be collected at baseline and 3, 6 and 12 months post-randomisation.Resource use, i.e. wound-related NHS consultations, support (e.g. occupational therapy, in home adaptations) and out-of-pocket costs, will be completed by the participant at baseline, 3, 6 and 12 months. Details of wound dressing changes (frequency and type) will be collected at weekly follow-up. Information on resources provided by the recruiting centre will be collected via a retrospective review of medical records at 12 months post-randomisation.

Additionally, data including demographics, comorbidities, smoking status, surgical procedure details (e.g. urgency, contamination level [20], type) and a wound photograph will be collected at baseline.

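### If death and amputation of the wound site are censored, the planned Kaplan-Meier curves overstate healing; cumulative incidence should supply the curves and medians

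*Protocol article*

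**What the plan says.** The Primary outcome section defines healing as "complete epithelial cover in the absence of a scab" and sets no condition on how that state is reached. The Statistical analysis section has the time "derived as the difference in days between randomisation and the first date of complete healing". It promises healing rates overall and by arm. It then names Kaplan-Meier for the curves and medians ("survival curves will be produced for the two groups and the median time to healing with a 95% CI presented") and, for the comparison, states: "A proportional hazards Cox regression model will be used to compare the healing times between the two groups".

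The Secondary outcomes section lists, among the clinical events recorded at the weekly calls, "re-operation (including skin grafting and closure surgery*), amputation and death". The text does not say how any of these enters the primary analysis, and it names no cumulative incidence estimate. Full analysis details are left to a statistical analysis plan that is not shown.

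Such events are foreseeable. Follow-up lasts 12 months, while the exclusion for poor prognosis reaches only "Life expectancy of less than 6 months". Foot and ankle wounds and leg wounds are stratification categories. The adverse event section makes specific provision for hospitalisation for limb amputation.

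**The concern.** Kaplan-Meier treats a censored participant as someone who remains at risk and will heal at the same rate as those still followed. That suits a participant lost to follow-up. It does not suit one who has died or whose wound site has been amputated, because that wound can no longer heal. Censoring there shares out those participants' unhealed probability among the people still at risk, so 1-KM exceeds the proportion who actually heal. It then describes a population in which nobody dies or loses the limb.

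What is at stake is the descriptive result that patients and clinicians read first: the healing curve, the proportion healed by 12 months and the median. The comparison between arms is much less exposed.

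**Working it through.** **Inputs from the protocol article.** Medians of 86 days (usual care) and 65 days (NPWT), 90% power, 12-month follow-up, 20% attrition and 696 participants (Sample size); "Significance tests will be two-sided at the 5% significance level" (Statistical analysis).

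**Step 1: the plan's own figure.** Take exponential healing times.
- Events (Schoenfeld): 4 × (1.960 + 1.282)² / [ln(65/86)]² = 537.
- Probability of healing by day 365: 1 − 2^(−365/86) = 0.947 in usual care and 1 − 2^(−365/65) = 0.980 in NPWT; mean 0.9634.
- Participants: 537 / 0.9634 = 557.4, and 557.4 / 0.8 = 697, against 696 stated.

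The design is reproduced by constant healing hazards with no competing event.

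**Step 2: add a competing event.** The healing hazards are l = ln 2/86 = 0.00806 per day (usual care) and ln 2/65 = 0.01066 per day (NPWT), a ratio of 1.323. Let m be the daily hazard of death or amputation of the wound site. It is assumed, and the same in both arms, because the documents give no rate.
- 1-KM with censoring at these events: 1 − exp(−365 l).
- Cumulative incidence of healing: l/(l+m) × [1 − exp(−(l+m) × 365)].
- Median from the cumulative incidence: −ln[1 − 0.5(l+m)/l] / (l+m).

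Example for usual care with m = 0.0005: l+m = 0.00856, l/(l+m) = 0.9416 and exp(−0.00856 × 365) = 0.0440, so the cumulative incidence is 0.9416 × 0.9560 = 0.900 against 1-KM of 0.947.

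The first two columns give m and the share of the usual-care arm with a competing event first by 12 months. Gaps are taken before rounding.

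| m per day | Share | Usual care: 1-KM / cumulative incidence | Gap (points) | Usual-care median (days) | NPWT: 1-KM / cumulative incidence | Gap (points) | NPWT median (days) |
|---|---|---|---|---|---|---|---|
| 0.000173 | 2.0% | 94.7% / 93.0% | 1.7 | 86.8 | 98.0% / 96.5% | 1.4 | 65.5 |
| 0.0003 | 3.4% | 94.7% / 91.9% | 2.9 | 87.5 | 98.0% / 95.5% | 2.5 | 65.8 |
| 0.0005 | 5.6% | 94.7% / 90.0% | 4.7 | 88.5 | 98.0% / 93.9% | 4.1 | 66.4 |
| 0.0008 | 8.7% | 94.7% / 87.4% | 7.3 | 90.0 | 98.0% / 91.6% | 6.4 | 67.3 |

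**Step 3: the difference between arms.** By 1-KM the 12-month difference is 98.0 − 94.7 = 3.2 points before rounding. By cumulative incidence it is 3.5, 3.6, 3.9 and 4.2 points down the rows, a change of 0.2 to 1.0 points. The difference in medians goes from 21 days to between 21.4 and 22.8 days.

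**Step 4: the Cox model and power.** Censoring at a competing event leaves the Cox model estimating the cause-specific hazard ratio. A simulation of 200,000 participants per scenario, in which closure surgery was censored at rates of 5% to 15% by arm, gave 1.32 to 1.33 in all six scenarios, against a true 1.323. With 5% of usual care having a competing event first, expected healing events among the 557 fall to 515 and power to 0.888.

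**Step 5: grafting and closure.** In the same simulation, counting closure as healing gave 1.32 when 5% of each arm had closure, 1.39 with 5% in usual care and 10% in NPWT, and 1.24 with those rates reversed. The handling matters when closure rates differ between arms.

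**The case against.** The strongest reply is that censoring rules are ordinary content of the analysis plan, which may already settle the point. Naming Kaplan-Meier does not rule out cumulative incidence there. This stands as far as the missing rule goes. It does not dispose of the point, because the protocol has already chosen the estimator for the curves and medians, and for a wound that can no longer heal a better one is available from events already recorded.

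Three further replies stand in full.
- The overstatement depends on censoring, which the text does not state. If a participant who dies is kept as unhealed to day 365 and follow-up is otherwise complete, Kaplan-Meier equals the cumulative incidence.
- The promised healing rates may be simple proportions, and censoring does not inflate those.
- Every event rate above is assumed. The earlier cohort's "further surgical procedures (16.8%) were all common" covers all procedures and does not count deaths, so it is not a rate of death or amputation.

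A reader might also infer that skin grafting and closure surgery are competing events, or that the hazard ratio is unreliable because of them. The documents do not support this. Healing is defined by epithelial cover whatever the route, so a grafted or closed wound can meet the endpoint, and treating closure as competing would change the endpoint. Planned delayed primary closure is excluded. The note belonging to the asterisk on closure surgery is absent from the extracted text and may bear on the matter. No section suggests coding such participants as never healed.

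**Conclusion.** The point holds for the Kaplan-Meier curves and medians, on the condition that death and amputation of the wound site are censored. With 2% to 9% of usual care having such an event first by 12 months, 1-KM is too high by about 2 to 7 points and the median too short by about 1 to 4 days in that arm. The NPWT arm is affected a little less, so the difference between arms moves by 1 point or less. These sizes rest on constant hazards, the design medians and a competing hazard that is equal in both arms.

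It would go too far to conclude that the primary comparison is biased: the Cox hazard ratio remains valid as a cause-specific hazard ratio. Nor is the sample size wrong, since 696 reproduces from the stated inputs and the loss of power at 5% competing events is about one point. An effect on the economic evaluation is possible, because trial evidence will inform that model, but the protocol does not say that Kaplan-Meier medians will be used in it.

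**What to change.** In the Statistical analysis section, and in the analysis plan:
- Replace the Kaplan-Meier curves with Aalen-Johansen cumulative incidence of healing by arm, with death and amputation of the wound site as competing events, and take the medians and their confidence intervals from it.
- Keep the Cox model as planned and label its result a cause-specific hazard ratio.
- Keep the stated endpoint, under which a grafted or surgically closed wound can count as healed, and add one sensitivity analysis that censors at skin grafting or closure surgery.

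The cost is a few sentences and a few extra analyses. The events are already collected at the weekly calls, so no new data are needed. The healed proportions and medians will look slightly less favourable than Kaplan-Meier with censoring would make them.

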#### Methods in analysis to handle protocol non-adherence and any statistical methods to handle missing data {20c}

To assess the impact of compliance on the primary outcome we will consider a complier average causal effect (CACE) analysis. This will produce an unbiased estimate of the treatment effect in the presence of non-compliance (defined as participants in the NPWT group who do not receive NPWT). Participants in the standard care group who receive NPWT will be considered as a cross-over.

For all outcomes, the level of missing data and the missing data mechanism will be assessed, and if required appropriate imputation techniques will be considered.

##### Economic analysis

The economic analysis will aim to evaluate the lifetime cost-effectiveness of NPWT, compared to all relevant comparators, in the treatment of SWHSI. The perspective of the cost-effectiveness analysis will be of the UK NHS and the Personal Social Services. The primary economic outcome will be the incremental cost-effectiveness ratio for NPWT vs usual care, expressed as cost per Quality Adjusted Life Years (QALYs) gained.

In addition, and to best assist decision-making, we will aim to build a de novo decision analytic model to establish which treatment is cost-effective, under current information. Evidence from the SWHSI-2 trial will be key to inform parameters of this economic model and the wider existing evidence base, identified through literature reviews, will also be used, including evidence from our previous cohort study [8]. When required and suitable, evidence synthesis techniques will be used to pool data to best inform specific decision model input parameters.

Regression approaches will be used to derive costs and health benefits (health utility measured using EQ-5D-5L), allowing for correlation between these as well as adjusting for key covariates. Alternative scenarios regarding the extrapolation of the primary outcome over the lifetime of the model, and the evidence informing it, will be explored. Uncertainty in the evidence base used to populate the decision analytic model will be characterised using appropriate distributions and uncertainty in the adoption decision will be demonstrated using probabilistic sensitivity analysis. The value of further data collection will be established using a value of information analysis.

Full details of the health economic analysis will be provided in a health economic analysis plan, which will be prepared prior to the completion of data collection.

##### SWAT analyses

For both SWATs, logistic regression will be used to assess the difference in binary outcomes, e.g. recruitment and retention rates. Factors used in the minimisation will be included as fixed effects in the analysis models for in the recruitment SWAT, with main trial allocation being adjusted for in the retention SWAT. For all analyses, site will be included as a random effect.

The difference in costs per recruited and retained participants will be calculated, including direct and indirect costs where applicable.

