#### SWAT outcomes

The primary outcome of the recruitment infographic SWAT will be the recruitment rate, i.e. the proportion of participants in each group who are randomised into the host trial. Secondary outcomes will include the proportion of patients in each group who are screened but do not go on to be randomised, and the cost-effectiveness of the intervention.

For the retention thank you card SWAT, the primary outcome will be questionnaire response rate, i.e. the proportion of participants who return their completed questionnaires at month 6 and 12 follow-up in each group. Secondary outcomes will include whether a reminder notice is required, completeness of response and cost of the intervention per participant retained.

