### Sample size {14}

To detect a 25% reduction in median time to healing (from 86 days with usual care to 65 days with NPWT), with 90% power, 12-month follow-up, and allowing for 20% attrition [8, 13, 21], 696 participants are required to be recruited and randomised (348 NPWT; 348 usual care).

A conservative estimate of a 25% decrease in median time to healing is used to derive this sample size, assuming a median time to healing of 86 days in the usual care group, which equates to a 21-day reduction in time to healing to 65 days in the NPWT group.

The 25% reduction in time to healing was selected on the following basis:
*Cost-effectiveness*. Models generated using observational data [8] suggest a 57.4% difference in time to healing would be required to demonstrate cost-effectiveness of NPWT. This should, however, be interpreted with caution given this relative effect is derived from observational data.*Current literature*. The average median time to healing in the control group of previous observational and randomised controlled trials is 86 days, with an average decrease in time to healing of 25% when NPWT is used [11–13, 22].*Significance to patients*. Patients are frequently disappointed by the slow healing process of a SWHSI and complete wound healing is therefore a major focus for patients [7]. Patient representatives have confirmed that the proposed reduction in time of 21 days with NPWT is likely to be significant for patients.

For the included recruitment and retention studies within a trial, as is usual with nested trials, a formal power calculation to determine sample size has not been conducted as the sample size is constrained by the number of patients approached about, or recruited into, the study, respectively.

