### Data collection and management

#### Plans for assessment and collection of outcomes {18a}

Data will be collected at baseline and at 3, 6 and 12 months post-randomisation, and via weekly clinical telephone follow-ups.

At baseline, epidemiological data will be collected including patient demographics, comorbidities, smoking status and surgical procedure details. Participants will complete a questionnaire comprising of a number of outcomes measures including surgical site infection (Bluebelle WHQ [17]), wound pain (using a visual analogue scale), quality of life (EuroQol EQ-5D-5L [19]) and resource use (using a bespoke, study specific questionnaire, which was designed based on the experiences learnt from the earlier feasibility study [27]).

At 3, 6 and 12 months, participants will be sent a postal questionnaire to complete and return comprising of a number of outcomes measures including surgical site infection (Bluebelle WHQ [17]), wound pain (using a visual analogue scale), health-related quality of life (EuroQol EQ-5D-5L [19]) and resource use (using a bespoke, study specific questionnaire). Where no response is provided after 2 weeks, a reminder questionnaire will be sent. If after 2 further weeks no response is received, a reminder telephone call will be made to the participant, and data collected by telephone if the participant is agreeable.

During the trial, participants will also be telephoned weekly to collect data on wound healing (using the criteria complete epithelial cover in the absence of a scab (eschar)), clinical events, treatment status and adverse events. When the participant reports that their treating healthcare professional has indicated that their wound is healed, and this has been confirmed in accordance with the SWHSI-2 trial definition (as above), the research nurse will undertake an assessment with the participant, ideally within 48 h of the report of healing being made, to confirm that the wound has healed. In the event wound healing has not been confirmed by a healthcare professional, the research nurse will first contact the clinical care team to obtain this confirmation and the date the participant was advised their wound was healed will be taken as the date of wound healing.

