#### Plans to promote participant retention and complete follow-up {18b}

With the study primary outcome being time to wound healing, if participants wish to withdraw involvement from the trial, we will seek, where possible, consent to obtain data on healing status from the participant’s treating healthcare professional. This should ensure attrition of the primary outcome data is limited.

To ensure we are able to collect as much participant reported questionnaire data as possible, a range of strategies will be employed. Firstly, if there is no response to a postal questionnaire after 2 weeks, a reminder letter and questionnaire will be sent. If there is still no response after a further 2 weeks, the participant will be telephoned to collect their data. In addition, if for any reason a questionnaire cannot be posted to the participant, the study team may contact the participant by telephone in order to complete data collection. Secondly, participants will be sent a pen with each follow-up questionnaire and will receive an unconditional £5 with both the 6- and 12-month questionnaires. Both strategies have been found to have an effect in improving participant retention and questionnaire response rates [28–30]. Participants will also be sent a study newsletter 2 weeks before the 6-month follow-up time point to encourage continued engagement.

A SWAT testing a thank you card is also embedded within the SWHSI-2 trial. Participants will be individually randomised to either receive a thank you card at months four and nine following recruitment or to receive no thank you card at these time points.

Many recruitment and retention strategies routinely include some element of thanks within them; however, there is little to no evidence to suggest these work. There is therefore a need to test the impact of thanks in the context of trial retention.

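### The retention SWAT model omits month-3 questionnaire return, a pre-card predictor already collected; adding it would give a minor gain in efficiency

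*Protocol article*

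**What the plan says.** The section on SWAT analyses sets out the model: "For both SWATs, logistic regression will be used to assess the difference in binary outcomes, e.g. recruitment and retention rates". The adjustment is stated as "with main trial allocation being adjusted for in the retention SWAT", and "For all analyses, site will be included as a random effect". No other section adds a covariate. Under sequence generation (16a), the retention SWAT is stratified by host-trial arm only.

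The primary outcome (SWAT outcomes) is "the proportion of participants who return their completed questionnaires at month 6 and 12 follow-up in each group". On the intervention, section 18b says: "Participants will be individually randomised to either receive a thank you card at months four and nine following recruitment". On the questionnaires, section 18a says: "At 3, 6 and 12 months, participants will be sent a postal questionnaire to complete and return". The month-3 questionnaire therefore has the same measures, postal route and reminder sequence as the two that define the outcome, and it is due before the first card. The blinding section (17a) says that participants are not told of the SWATs.

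The sample size section gives no power calculation for the SWATs, because "the sample size is constrained by the number of patients approached about, or recruited into, the study, respectively".

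**The concern.** Month-3 return is the only postal questionnaire return observed before any card is sent. Someone who sent back one questionnaire is plausibly more likely to send back the next, so it is the natural baseline covariate for later return. The card cannot influence it: none has been sent, and participants do not know their SWAT allocation. Month-6 return cannot play this part for month 12, because it follows the first card.

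The host trial caps the number of participants, so an efficient analysis is the main way left to gain power. A null result with a wide interval would say little about whether thanking participants helps retention, which is the question the SWAT is meant to answer.

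**Working it through.** **1. Timing.** Month 3 falls at about day 91. Reminders run at 2 weeks and 2 weeks later (section 18a), so the telephone call falls at about 91 + 28 = day 119. Month 4 is about day 122. Month-3 status can be fixed before the card is sent, but the margin is only a few days.

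**2. Ceiling on SWAT size.** The article gives no SWAT figure to reproduce, but the host figure of 696 can be checked. With hazard ratio 65/86 = 0.756, two-sided 5% and 90% power, the Schoenfeld formula gives 4(1.960 + 1.282)²/(ln 0.756)² = 537 events. Exponential healing over 12 months averages 0.963, so 537/0.963 gives 558 participants, and 558/0.80 gives 698, against 696 stated. I take 696 as the most the SWAT can have, 348 per arm.

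**3. Power without the covariate.** The return rates are assumptions, as the article gives none: 80% without the card, 85% with it.
- SE of the difference = √[(0.80×0.20 + 0.85×0.15)/348] = 0.0287.
- z = 0.05/0.0287 = 1.74; power = Φ(1.74 − 1.96), about 41%. With 556 participants it is about 34%.

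**4. Expected gain.** Let phi be the correlation between month-3 and later return. With month-3 return r, later return p₁ among month-3 responders and p₀ among non-responders, and overall later return p, phi = (p₁ − p₀)√[r(1−r)/(p(1−p))]. Adjustment multiplies the variance of the rate difference by roughly 1 − phi². With r = p = 0.80, phi is simply p₁ − p₀:
- 0.85 − 0.60 = 0.25, factor 0.94
- 0.90 − 0.40 = 0.50, factor 0.75
- 0.95 − 0.20 = 0.75, factor 0.44

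**5. Simulation.** 2,000 trials per scenario, N = 696. Return is regressed on card and host arm, without and then with month-3 return.

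| phi | Power at +5 points | Power at +8 points | Variance ratio of rate difference (+5) | Type I error |
|---|---|---|---|---|
| 0.25 | 41% → 42% | 81% → 84% | 0.92 | 5.6% → 5.5% |
| 0.50 | 41% → 52% | 81% → 90% | 0.75 | 4.8% → 4.8% |
| 0.75 | 42% → 71% | 83% → 98% | 0.51 | 5.3% → 4.9% |

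A separate simulation (N = 696, about 76–80% return, +5 points) gave 43% → 45% at phi 0.25, 43% → 52% at 0.50 and 37% → 57% at 0.66, again with type I error near 5%.

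**6. The odds ratio scale.** At phi 0.50 and +5 points, the mean log odds ratio moves from 0.352 to 0.463 and its SE from 0.202 to 0.234. The ratio of estimate to SE goes from 0.352/0.202 = 1.74 to 0.463/0.234 = 1.98. Power rises because the conditional estimate moves away from zero by more than its SE grows. The interval for the log odds ratio itself becomes wider.

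**7. Limits.** The site random effect was not simulated, and month 12 was not simulated separately.

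**The case against.** The strongest reply is that the planned model is sound. It carries the factor used to stratify the SWAT randomisation, adds site, and is valid. The article defers full statistical detail to an analysis plan that is not shown, and that plan could add the covariate. This stands as far as it goes: the point is an improvement to the adjustment set that the article states, not an error in it.

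Three further objections also stand in part.
- The gain rests on an assumed correlation and is trivial if that is weak. Month 3 is not quite like the later time points: section 18b attaches a £5 payment to months 6 and 12 only, and sends a newsletter shortly before month 6. Either could weaken the correlation.
- The month-3 telephone reminder falls close to the first card, so late month-3 responses could follow it. A cut-off is needed.
- The outcome is a proportion in each group, a marginal quantity, while the adjusted odds ratio is conditional on month-3 return. Reporting a standardised rate difference answers this.

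Stronger readings are not supported. A reader might infer that leaving the covariate out biases the odds ratio towards 1. The two models estimate different odds ratios, marginal and conditional (non-collapsibility), and the planned test keeps its type I error. A reader might also hold the conditional odds ratio at 1.6, see unadjusted power fall from 55% at phi 0.30 to 30% at phi 0.66, and blame the omission. Most of that fall arises because the true rate difference in those scenarios shrinks from about 6.0 to about 4.5 points. With the difference held at 5 points in the table above, unadjusted power stays at 41–42%.

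**Conclusion.** The point holds as a minor efficiency improvement to a nested study. The stated model leaves out a valid pre-card predictor that the trial already collects. At 696 participants, about 80% return and a 5-point effect, including it adds about 2 points of power at phi 0.25 and about 10 at phi 0.50, with larger gains above that. The variance of the rate difference falls by roughly 1 − phi² as a proportion of its unadjusted value. Return rate, effect size and correlation are all assumptions. There is no gain in precision for the log odds ratio, no bias in the planned test, no contradiction between sections, and no bearing on the host trial's question.

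**What to change.** In the section on SWAT analyses, add month-3 questionnaire status as a fixed effect in the retention models for months 6 and 12, and keep host-trial allocation and the site random effect. Define status as returned or not returned by a fixed date before the month-4 card is sent, identical in both SWAT arms, and state whether data taken by telephone count as returned. Alongside the odds ratio, report the covariate-standardised difference in return rates with its 95% CI.

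The cost is a sentence or two of analysis text and one covariate already held; no new data are needed. The downside is that the adjusted odds ratio becomes conditional on month-3 return, which is why the standardised difference should accompany it. The article reports 252 of 696 participants recruited, so at that stage the change could still be specified before the SWAT data are analysed.
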